## Abstract

**Purpose.:**

Sodium glucose co-transporter 2 inhibitors (SGLT2i) remarkably reduced the incidence of hospitalization for heart failure and cardiovascular death of conservatively managed chronic kidney disease. We hypothesized that adding SGLT2i to standard treatment would yield cardiovascular benefits also in end-stage kidney disease (ESKD) individuals on dialysis.

**Methods.:**

The DARE-ESKD-2 Trial (NCT05685394) is an ongoing, single-center, open-label, controlled trial aimed at assessing the cardiovascular effects of dapagliflozin in ESKD on dialysis. Eligible patients are adults on renal replacement therapy for more than 3 prior to enrollment. Exclusion criteria encompass pregnancy, liver failure, and current use of a SGLT2i. After signing an informed consent form, participants are randomized 1:1 to either dapagliflozin 10mg PO plus standard treatment or standard treatment alone for 6 months. Echocardiogram, anthropometry, blood sample collection, 6-min walk test, gait speed, and Kansas City Cardiomyopathy Questionnaire (KCCQ), are performed at baseline and at study termination. Participants are contacted monthly during treatment for outcomes disclosure. The primary endpoint of our study is the between-groups differences in posttreatment changes in plasma levels of N-terminal pro-B natriuretic peptide. Secondary endpoints include the differences between groups in the changes of echocardiography measurements, cardiopulmonary tests performance, body composition. The incidence of safety endpoints will also be diligently compared between study arms.

**Conclusion.:**

The DARE-ESKD-2 trial will provide unprecedented data on the cardiovascular safety and efficacy of SGLT2i in ESKD individuals on dialysis. This study will pave the grounds for improving clinical outcomes of dialysis recipients.

## INTRODUCTION

Current estimates project a troubling scenario: the prevalence of end-stage kidney disease (ESKD) requiring renal replacement therapy (RRT) is expected to soar to a staggering 15 million before 2030.^1^ This figure is particularly alarming when we consider that these patients face a 20-fold higher risk of major cardiovascular events compared to individuals with preserved renal function. These events currently account for six out of every ten deaths within the already concerning 20% annual mortality rate associated with RRT.^2^ This grim reality stems from a well-stablished cardiorenal interplay, where deteriorating kidney function triggers a cascade of multisystem organ dysfunction. This chain reaction ultimately leads to heart failure, disautonomia, hypertension, and atherogenesis, all of which contribute to the substantial cardiovascular burden experienced by those undergoing dialysis.^2,3^

Despite these statistics, individuals with ESKD have been excluded from landmark clinical trials investigating inhibitors of the sodium glucose cotransporter 2 (SGLT2i), which consistently demonstrated significant cardiorenal protection.^4^ In fact, both in DAPA-CKD and EMPA-KIDNEY trials, SGLT2i treatment led to a remarkable one-third reduction in the incidence of a composite outcome comprising cardiovascular death and heart failure hospitalization among individuals with chronic kidney disease (CKD) stages 3 to 4.^5,6^ From the mechanistic perspective, these benefits were primarily attributed to natriuresis and glycosuria, which contributed to improved volume and glycemic controls.^7^ Nevertheless, as our understanding has deepened, evolving evidence has unveiled a plethora of other advantageous effects associated with SGLT2i treatment. These effects extend beyond kidney function and encompass enhancements in endothelial function, myocardial energy metabolism, and the mitigation of dysautonomia.^8^ Consequently, SGLT2i emerges as a promising therapeutical target for preventing cardiovascular morbidity, even in individuals with severely impaired kidney function who require dialysis.^9^

In this scenario, having outlined the safety profile and pharmacokinetics of dapagliflozin in dialysis, we hereby present the study design for the DARE-ESKD-2 trial, which aims to explore the cardiovascular effects of dapagliflozin in ESKD.^10^ The primary objective of this study is to investigate whether dapagliflozin influences cardiac remodeling markers. Secondarily, this study aims to explore its potential role also on cardiopulmonary performance, quality of life, adiposity, and bone metabolism. The data gleaned from this study could also serve as a foundation for future mechanistic hypothesis generation and assessments aimed at long-term prevention of major cardiovascular events.

## METHODS

### Study design and population

The DARE-ESKD-2 study (NCT05685394) is an ongoing randomized, phase 3, controlled, open-label trial aimed at assessing the cardiovascular effects of dapagliflozin vs. standard treatment in individuals with ESKD who are undergoing dialysis. The study protocol received ethical approval from the local ethics committee, and it complies with the principles outlined in the Declaration of Helsinki.^11^ Eligible participants are adults aged 18 years or older who have been on regular hemodialysis or peritoneal dialysis for at least three months prior to enrollment. Exclusion criteria encompass hypersensitivity to any components of the study drug, pregnancy, impaired liver function, recent use of SGLT2i, or experiencing acute coronary syndrome within the three months preceding randomization.

### Clinical care protocol

The study protocol, outlined in Fig. 1, begins with patient referrals from local dialysis clinics to our research center, where undergo their initial medical assessment to determine eligibility. During this visit, a certified physician presents the informed consent form and conducts a thorough interview to gather medical history register, followed by a comprehensive physical examination. Then, participants are randomly assigned in a 1:1 ratio either dapagliflozin (10mg/day) plus standard treatment or standard treatment alone (control group) using an automated system.

Furthermore, peripheral blood samples are collected for biochemical analysis, and a 12-lead electrocardiogram is obtained. Blood pressure readings are taken in triplicate after 3 minutes of rest in a seated position and repeated after 1 minute of standing to assess orthostatic changes, using the Omron Hbp-1120 device (Omron Healthcare, Japan). Additionally, assessments through dual X-ray absorptiometry (DXA), bioimpedance, echocardiography, gait speed measurement, and six-minute walk test are performed during this visit.

Once the baseline evaluation is completed, patients in the dapagliflozin group receive the necessary pills for a 24-week treatment period, and all participants are thereupon contacted monthly to report outcomes and monitor medical adherence until study’s conclusion, at which baseline evaluations are repeated.

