### Kansas City Cardiomyopathy Questionnaire

The Kansas City Cardiomyopathy Questionnaire (KCCQ) comprises a 23 self-administered questions, addressing a wide range of physical, psychological, and social symptoms that may arise from heart failure.^22^ The KCCQ yields scores on a scale of 0 to 100 points, where higher scores correspond to a better quality of life.^22^ Study participants fill the Portuguese-validated KCCQ prior to randomization and at the study conclusion.^23^

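### As written, randomisation appears to precede every baseline test except the KCCQ, so in this open-label trial participants may know their arm when the effort-dependent baselines are taken

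*Protocol article*

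**What the plan says.** The trial is described under Study design and population as an "ongoing randomized, phase 3, controlled, open-label trial".

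The Clinical care protocol section narrates one visit. Consent, interview and physical examination come first. The next sentence is "Then, participants are randomly assigned in a 1:1 ratio". The following paragraph opens with "Furthermore, peripheral blood samples are collected for biochemical analysis, and a 12-lead electrocardiogram is obtained", goes on to blood pressure, and ends by saying that "assessments through dual X-ray absorptiometry (DXA), bioimpedance, echocardiography, gait speed measurement, and six-minute walk test are performed during this visit". The last step is dispensing: "Once the baseline evaluation is completed, patients in the dapagliflozin group receive the necessary pills".

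The abstract has the same order: "After signing an informed consent form, participants are randomized 1:1", with the baseline tests named in a later sentence.

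One measure is timed explicitly. The Kansas City Cardiomyopathy Questionnaire section says: "Study participants fill the Portuguese-validated KCCQ prior to randomization and at the study conclusion". No other baseline measure carries such a statement.

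The Statistical analysis section compares changes from baseline by ANCOVA or its rank version, with the baseline value and study arm in the model, on an intention-to-treat basis in all randomised participants.

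**The concern.** A baseline is useful as a covariate because it cannot have been influenced by the allocation. If the participant already knows the arm, that protection is lost for any test that depends on effort. Under Cardiopulmonary functional testing, the walk test and the 4-metre gait speed ask for the participant's fastest walking, and handgrip is the best of three attempts. All three are secondary endpoints. A participant disappointed or encouraged by the allocation could perform differently at baseline, and there is no placebo to hide the arm.

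The second issue is attrition. If blood is drawn after randomisation, someone who withdraws on learning the arm counts as randomised but has no baseline NT-proBNP. That person has no observed change for the primary endpoint, although the plan promises a comparison of everyone randomised.

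**Working it through.** **Step 1: what the sections establish about order**

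| Section | Evidence | What it supports |
|---|---|---|
| Clinical care protocol | Examination, *Then* randomisation, then the tests, then pills once baseline is complete | Randomisation before the tests |
| Clinical care protocol | Blood and ECG joined by *Furthermore*, imaging and walking tests by *Additionally* | Additive words; order implied only |
| Abstract, Methods | Randomisation after consent, tests named later | Same order, but it names the KCCQ among the later tests |
| KCCQ section | KCCQ expressly before randomisation | The only explicit pre-randomisation timing; it also shows that order of mention in the abstract is not strict chronology |

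No section says that the blood, imaging or walking tests come before randomisation. Handgrip is not listed in the visit narrative at all, so its timing is inferred from the tests it accompanies. Figure 1 was not available.

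**Step 2: who could know the arm**

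Evaluators are said to be blinded for echocardiography (Echocardiography; Discussion), DXA (Body Composition), and cardiopulmonary tests and biochemistry (Discussion). Participants are not blinded. The article does not say when they are told their arm, and it describes no step that withholds it until testing is finished.

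**Step 3: which endpoints are exposed**

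Study drug is handed out only after the baseline evaluation, so no baseline value reflects drug exposure. NT-proBNP, DXA and echocardiographic values should hardly respond to knowing the arm during the same visit. That leaves three of the eight secondary endpoints: walk distance, gait speed and handgrip.

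**Step 4: size of the bias if a shift occurs**

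The plan gives no figure for this, so there is none to reproduce. Let the recorded baseline in one arm be displaced by d, with no true treatment effect, and let β be the slope of follow-up on baseline.

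- ANCOVA effect = (difference in follow-up means) − β × (difference in baseline means) = 0 − βd = −βd. Modelling the change with baseline as covariate gives the same arm coefficient.
- Unadjusted change score: 0 − d = −d.

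With β and d both assumed, the absolute ANCOVA bias for the walk test is:

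| β | d = 10 m | d = 20 m |
|---|---|---|
| 0.5 | 5 m | 10 m |
| 0.8 | 8 m | 16 m |
| 0.9 | 9 m | 18 m |

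The bias runs opposite to the shift, whose direction is unknown.

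**Step 5: effect on false-positive rate**

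This is a simulation of 4,000 trials per row. It uses 40 per arm (the planned 80 split 1:1), no true effect, an assumed baseline to follow-up correlation of 0.8, and the baseline lowered in one arm.

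| Shift (SD) | ANCOVA bias (SD) | ANCOVA type I error | Change-score type I error |
|---|---|---|---|
| 0 | 0.00 | 5% | 5% |
| 0.1 | 0.08 | 9% | 11% |
| 0.2 | 0.16 | 21% | 28% |
| 0.3 | 0.24 | 40% | 55% |

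The simulated biases agree with βd (0.8 × 0.1 = 0.08, 0.8 × 0.2 = 0.16, 0.8 × 0.3 = 0.24). Baseline adjustment therefore reduces this bias only slightly relative to a raw change score. Neither calculation shows that a shift happens.

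**The case against.** The strongest reply is that the order is never stated. The linking words are additive, the abstract's own sequence is contradicted for the KCCQ, the visit narrative is incomplete, and a figure that might settle it was not seen. Being assigned by an automated system is also not the same as being told. The only arm-revealing act with a stated time is dispensing, and that follows baseline. This stands in part: the sequence must be reported as implied and the time of disclosure as unknown. It does not remove the need for a correction, because the text read naturally puts randomisation first and nothing in it says otherwise.

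A reader might infer that allocation was known to everyone in the room and that every baseline, including NT-proBNP, is compromised. The documents do not support that. Evaluators are said to be blinded, and nothing shows that this blinding fails. No drug precedes baseline, and laboratory and imaging values give little scope for a change in effort. Evaluator blinding does not, however, stop an unblinded participant from walking faster or slower.

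It is also fair that participants know their arm at the final walk test, so reordering the baseline does not remove performance bias at follow-up. It removes only the part that enters through the covariate.

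On attrition, no withdrawal between allocation and blood sampling is reported. A missing baseline might be handled by imputation, and an unseen analysis plan may cover that. The point is only that such losses are avoidable by design.

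**Conclusion.** The point holds in a limited form, and its severity is moderate. As written, randomisation appears to come before all baseline tests except the KCCQ, and participants may know their arm when walk distance, gait speed and probably handgrip are first measured. If that knowledge shifts baseline by d in one arm, the planned ANCOVA carries a bias of about −βd into those secondary endpoints. The metre and type I error figures illustrate sensitivity under assumed β, correlation and d; the actual size and direction are unknown.

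For the primary endpoint, the measured NT-proBNP values are hardly affected. The exposure there is limited to participants who leave after allocation and before blood sampling, and their number is not given. The stated sample sizes of 52 and 80 do not change.

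The conclusion rests on two readings: that the visit narrative is chronological, and that allocation is disclosed to participants when it is made.

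**What to change.** Revise the Clinical care protocol section, and Figure 1 if it shows the same order, to say that all baseline assessments (blood, KCCQ, echocardiography, DXA, bioimpedance, walk test, gait speed, handgrip) are completed and locked in REDCap before the automated system releases the allocation, with dispensing after that as now. Apply this to all remaining participants. If it is already the practice, correcting the text is enough.

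For participants already enrolled, record for each baseline test whether it came before or after allocation, using REDCap's audit records where they allow it, and report the order as a limitation. Add a sensitivity analysis by order for walk distance, gait speed and handgrip only if enough participants have pre-allocation baselines. If randomisation has always come first, that subset may be almost empty and the analysis uninformative. Report how many participants left between allocation and blood sampling, by arm.

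The cost is small, since all steps already fall within one visit. The drawback is a change of visit order part-way through an ongoing trial, which leaves two procedural cohorts; the date of the change should be recorded so that they can be told apart.

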### Echocardiography

Transthoracic echocardiogram is performed by experienced cardiologists blinded to patients allocation and comply with the latest recommendation from the American Society of Echocardiography.^12^ Heart ultrasound images are obtained by an equipment with three-dimensional (3D) technology (Philips EPIQ CVX ultrasound system, Philips Medical Systems, Andover, MA, USA) and a transducer for real time multiplanar volumetric analysis (X5–1 xMATRIX array transducer with PureWave crystal technology, 3040 elements, 5 – 1 MHz). Cardiac chambers diameters, volumes, indexed left ventricle (LV) mass estimation and LV ejection fraction are analyzed by both 2D and 3D methods (*HeartModel*^A.I^., Philips Medical Systems, Andover, MA, USA).

Complete echocardiographic analysis included appearance of the thoracic aorta, analysis of cardiac flows and presence of valvular heart disease. Diastolic function analysis followed the latest guidelines and included the E/e’ ratio, calculated from mitral inflow E velocity and mean tissue Doppler myocardial e’ velocity from mitral annulus (septal, lateral, anterior, and inferior) as an indirect estimation of the left atrium pressure. Global longitudinal strain by speckle tracking used a dedicated automated tool (Automated Cardiac Motion Quantification^A.I^., aCMQ^A.I^.,Philips Medical Systems, Andover, MA, USA).^13,14^

### Body Composition

Body composition is evaluated using a DXA device (Lunar iDXA enCore version 13.60, GE Healthcare, USA) administered by an accredited anthropometrist who is blinded to participant allocation. Image acquisition and standardization of region of interest comply with the latest guidelines set forth by the International Society for Clinical Densitometry. The equipment undergoes weekly calibration for accuracy.^15^ This examination yields data on lean and fat mass as well as bone mineral density with the respective scores at specific anatomical sites including the femoral neck, Ward’s triangle, trochanter, and lumbar spine.. In case where patient find it challenging to fit into the equipment, an image mirroring technique is employed.^16^

During the same assessment, we utilize bioimpedance analysis (Model-450, Biodynamics Corporation, Seattle, WA, USA) to obtain information on resistance, reactance, estimated basal metabolic rate, fat mass percentage, lean mass, body water, and phase angle. These measurements are analyzed inconsideration of body mass, age, and gender.^17^ As part of our comprehensive evaluation, we also obtain data on weight, height, and arm circumference according to validated protocols.^18,19^

#### Cardiopulmonary functional testing

The 6-minutes’ walk test (6MWT) adheres to the guidelines set forth by the American Thoracic Society.^20^ Briefly, participants are instructed to maintain their swiftest walking pace without running in a demarcated corridor for precisely 6 minutes, with supervision provided by a researcher responsible for registering the distance traversed.^4^ Readings for pulse oximetry, blood pressure, and heart rate are registered prior to commencing the test and immediately after it is terminated. Following the conclusion of the test, patients convey their perceived effort level using the Borg Scale.^4^ The 6MWT is contraindicated for patients with a resting heart rate exceeding 120 beats per minute, or a systolic or diastolic blood pressure exceeding 180mmHg and 100mmHg, respectively. Subsequently, patients are instructed to walk at their maximum pace within the same corridor, while the evaluator register the time taken to cover a precisely marked 4-meter distance. This evaluation is conducted three times, and the best time out of the three trials is utilized for analyzing 4-meter gait speed.

Additionally, handgrip strength is assessed in triplicate using a hand dynamometer (SH5001, Saehan Corporation, Dangjin-gun, South Korea), and the best result out of the three measurements (in Kg) is employed in our analysis.^21^

### Kansas City Cardiomyopathy Questionnaire

The Kansas City Cardiomyopathy Questionnaire (KCCQ) comprises a 23 self-administered questions, addressing a wide range of physical, psychological, and social symptoms that may arise from heart failure.^22^ The KCCQ yields scores on a scale of 0 to 100 points, where higher scores correspond to a better quality of life.^22^ Study participants fill the Portuguese-validated KCCQ prior to randomization and at the study conclusion.^23^

### Biochemical analysis

Peripheral blood samples are collected and dispatched to the clinical analysis laboratory for a comprehensive panel of tests. These tests include a complete blood count (flow cytometry and impedance – DXH 800), urea (urease with GLDH), creatinine (kinetic – IFCC), sodium, calcium, phosphate, and potassium (Selective Electrode), venous blood gases (Sensor-OMNI), aspartate aminotransferase (AST) and alanine aminotransferase (ALT) (kinetic – IFCC), and alkaline phosphatase (Abcam, Cambridge, UK).

To facilitate enzyme immunoassays, blood samples are collected and centrifuged at 3,500 rpm for 10 minutes. Plasma aliquots are cryopreserved in liquid nitrogen for subsequent measurements of N-terminal pro-B natriuretic peptide (NT-proBNP, Human pro-BNP Georgia, USA), fibroblast growth factor-23 (FGF-23; Abcam, Cambridge, UK), and parathyroid hormone (Sigma-Aldrich, San Luis, Missouri, EUA), α-Klotho (Quidel, San Diego, USA), and MILLIPLEX MAP Human Bone Magnetic Bead Panel - Bone Metabolism Multiplex Assay (Merck, Darmstadt, Germany). These quantitative measurements are performed in accordance with the manufacturer’s recommendations, and the absorbance is determined using a microplate reader (Biotek EPOCH 2).

### Follow-up

Following randomization, participants receive monthly phone calls over a six-month period. During each contact, they are queried about various aspects, including changes in their dry weight, alterations in bowel and urinary habits, their overall well-being during daily activities, blood pressure measurements, occurrences of fractures, any medical procedures undergone, initiation of new treatments, surgeries, hospitalizations, infections, and clinical incidents. Additionally, participants in the dapagliflozin group are required to report the number of study drug pills taken in the past 30 days to track medication adherence, which is registered as a percentage.

### Efficacy endpoints

The primary endpoint of our study is the between-groups differences in posttreatment changes in plasma levels of NT-proBNP. Secondary endpoints encompass the differences between groups in the changes of LV mass, EF, E/e’ ratio, KCCQ points, 6-min walk test distance, gait speed, lean to fat mass ratio, and handgrip strength.

In addition, an exploratory analysis will be conducted, in which participants with residual diuresis will be inquired about changes in their urinary output. Furthermore, the incidence of a composite outcome comprising cardiovascular death, hospitalization for heart failure, and stroke will be compared between the dapagliflozin and control groups. Changes in serum levels of bone metabolism markers, such as FGF-23 and a-Klotho, as well as on bone mineral density, will be compared between groups as an exploratory analysis.

